##### Implementation fidelity audits

Data will be analysed using descriptive statistics to determine the level of implementation fidelity. This process of evaluation will be conducted to assess for fidelity and success of implementation across sites [56, 57]. Fidelity controls will be deployed for internal and external validity of implementation and measured through audits and implementation logs.

##### Handling of missing data

Missing data will be addressed using appropriate imputation methods, informed by the pattern of missingness (e.g. whether data are missing at random or not). Sensitivity analyses will be conducted to assess the robustness of findings, including complete-case analysis and the use of alternative imputation strategies if patterns of missingness suggest potential bias. Additional analyses per protocol may also be applied to further examine the robustness of results.

#### Data management

##### Data storage and access

Data will be managed in accordance with NSW Health research data management policy and procedures. All data will be kept for a minimum of 15 years post-publication, in accordance with the 2018 National Health and Medical Research Council (NHMRC) Australian Code for the responsible conduct of research and accompanying guides [58].

##### Data de-identification and linkage

Research nurses at the study site will have access to eMR data, used to identify patients that meet study inclusion criteria and determine those patients that require medical record review and/or rapid response review. Only site researchers will have access to their identifiable site data. Once data collection is complete, all data will be imported into Excel and then integrated using the identifiers of MRN, name and age. These three identifiers are required to maximise the likelihood of correctly matching patients between datasets.

### Ethics and dissemination

#### Data monitoring

A Data Monitoring Committee will not be required for this trial due to the absence of significant blinding and the relatively low-risk nature of the intervention. Trial Steering and Investigator Committees will be established to oversee the study which includes the chief investigator, site leads, and consumer representatives. Any decision to modify or terminate the trial will be made collaboratively by the Steering and Investigator Committees in consultation with the trial sponsor and ethics committee. The Chief Investigator, supported by a project manager and site staff will manage daily operations including recruitment, data handling, stakeholder engagement and reporting. The project statistician will monitor data to ensure consistency. Data entered by research officers into REDCap™ will undergo automated plausibility checks (i.e. acceptable value range, detection of invalid characters) and regular audits. The University of Sydney will be the coordinating centre.

#### Harms

While participants are not expected to experience adverse effects from direct involvement in the study, provisions are in place to address any emotional distress that may arise. Should a participant become emotionally distressed during survey or focus group participation, the activity will be ceased immediately. Support will be offered including referral to their General Practitioner or appropriate support services such as Beyond Blue, Lifeline, or 13YARN. The research nurse will assist in arranging support if needed.

Adverse events will be managed according to site procedures and reported in line with NHMRC Guidance on Safety Monitoring and Reporting guidelines and the University of Sydney’s Safety Reporting Guidelines 2021. The chief investigator, along with site investigators, will collect, oversee documentation and reporting. Serious adverse events will be reported to the University of Sydney Clinical Trial Support Office, the relevant hospital governance office and escalated to the Trial Steering Committee for review and management.

#### Dissemination

Irrespective of the outcome, the findings will be shared through various platforms, including open-access peer-reviewed journals, conference presentations, and local, national, and international forums. Authorship for publications will be determined prior to submission and will adhere to the International Committee of Medical Journal Editors’ guidelines for peer-reviewed works [59]. Anticipating intervention efficacy, the results will be communicated to relevant national agencies and stakeholders to influence nursing practice, health policy, and nurse education.

## Discussion

HIRAID® Inpatient aims to optimise nurses’ contribution to the quality and safety of hospital care nursing care by preventing adverse events, improving patient experiences and strengthening clinical communication through a standardised, evidence-informed framework for assessment, decision-making and action. Study strengths include methodological design, theoretical foundations, and implementation strategies that will be underpinned by evidence derived from the development, refinement and implementation of HIRAID® in the ED [7] and aged care settings [32]. Hospital inpatient wards provide care that is often long-term, with a focus on ongoing treatment plans and recovery. This differs from the ED, where care is provided rapidly in a fast-paced environment, and aged care facilities where the focus of care is on managing enduring health conditions and supporting activities of daily living. However, all care settings share commonalities as they are complex, resource-constrained environments that require person-centred care, clear communication and adherence to standards and policies. The experience and insights gained from implementing HIRAID® in other settings will provide a foundation for approaches to increase the likelihood of successful and sustained implementation.

A diverse sample of specialty wards within hospitals of different delineations, including rural, regional and metropolitan hospitals, will be engaged in this study to maximise the generalisability of findings and provide insights relating to the site-specific needs, adaptations and considerations. The incremental implementation of the stepped-wedge design is well-suited to the evaluation of health service outcomes and practical to implement [30]. By each cluster contributing data to both control and intervention phases, the risk associated with comparing heterogeneous hospitals is mitigated. Additionally, geographical separation minimises the risk of contamination between clusters/sites.

### Methodological considerations and risks

The study requires substantial commitment from healthcare partners, including the co-design, implementation, maintenance, and evaluation of HIRAID® Inpatient. Following success in the ED, nursing management advocated for HIRAID® adoption in the hospital inpatient setting. However, input and engagement from frontline nurses must be considered. In addition to Phase 2 surveys and focus groups, an assessment of current documentation, education and orientation practices in specialty wards will be conducted to engage nursing staff and address inherent challenges unique to these diverse patient care settings.

Due to the nature of the intervention, blinding will be limited. While recipients will be blinded to cluster order, they cannot be blinded to the transition from control to intervention conditions, introducing a risk of bias in self-report measures (e.g. nurses’ perceived confidence). For non-self-reporting measures (e.g. clinical deterioration events), objective assessment and repeated measurements across baseline and post-intervention periods mitigate bias. To minimise bias, assess long-term outcomes and detect relapse effects, most outcome measures will be collected for a range of 3–12 months post-intervention.

The application of HIRAID® to a ward context poses a delivery risk. To manage this, pre-implementation diagnostics will identify potential issues, and solutions will be incorporated into the site-specific implementation plans. Implementation research nurses will escalate and manage challenges through a hospital working group and research management group.

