### Phase 3: Implementation evaluation of HIRAID® Inpatient

#### Study design

In Phase 3, the HIRAID® Inpatient framework will be implemented using a Type II effectiveness-implementation hybrid design [29], including a SW-cRCT [30]. The hybrid approach allows testing of the implementation strategy at the same time as observing the outcomes of the intervention [29, 30]. Four clusters will be progressed through three sequential phases: control, intervention transition and post-intervention, with a staggered rollout and a 1:1 allocation ratio, with most data collected from each defined population as outlined in Table 4. The trial is structured within a superiority framework, aiming to demonstrate improved outcomes compared to usual care.

Each participating hospital ward (cluster) will begin in the control phase, representing a period of routine or usual care before the scheduled implementation of the HIRAID® Inpatient framework. During this phase, baseline data and behavioural diagnostics will be collected to serve as the comparator for the intervention. Rather than using a separate, concurrent control group, this SW-cRCT uses each cluster as its own control. Data gathered during the pre-intervention phase will be directly compared with data collected post-implementation. This design enables evaluation of the intervention against established, real-world clinical practice. The HIRAID® Inpatient intervention will then be implemented over a three-month period (Intervention Transition), followed by an intervention data collection period, lasting between 3 and 12 months, depending on the cluster (Fig. 3).

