**Fig. 3 Fig3:**
[figure not shown]
The stepped-wedge cluster randomised controlled trial design for the implementation of HIRAID® Inpatient across four clusters. Each sequence comprises a 3- to 12-month baseline control condition, a 3-month intervention transition period, and a 3- to 12-month intervention exposure condition

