#### Randomisation

Each cluster will be randomly allocated to one of four starting dates for implementation. Randomisation will be performed by the study statistician using computer-generated numbers. Participating wards will have no influence over the allocation prior to randomisation, ensuring concealment of the allocation sequence until wards are assigned. No further changes to clusters will be made once the allocation has been finalised to minimise the risk of bias.

We are unable to randomise sites to clusters because of geographical location and clinical governance. The significant geographical distance between sites, mitigates the risk of contamination due to reduced proximity. Randomising clusters based on health service provides consistent clinical governance for study operations.

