#### Statistical methods

##### HIRAID® effectiveness/clinical outcomes

Survey and health record data collected for implementation evaluation will be analysed using descriptive statistics to assess fidelity levels and feedback from study sites. Descriptive statistics will be calculated using the chi-square test for categorical variables, and the *T*-test (normally distributed data) or the Mann-Whitney *U* test (non-normally distributed data) for continuous variables. All analyses will follow the intention-to-treat principle, with all clusters evaluated according to their original group allocation, regardless of adherence or protocol deviations. Comparisons within and across clusters will be conducted using the generalised linear mixed model (GLMM) approach, applying appropriate link functions tailored to each outcome variable. For binary outcome measures, a GLMM with a binary logistic link function will be used, while for count outcome measures, GLMMs with Poisson or negative binomial link functions will be applied. The model will account for the random effect of the cluster and will adjust for relevant confounders, identified in the descriptive analyses, as fixed effects. SPSS V28™ (IBM Corp., Armonk, NY, USA) will be used and the alpha set to < 0.05 [18].

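### The 3–12 month follow-up is said to detect relapse, but the analysis described has no time-since-rollout term, and exposure beyond month 6 rests on two clusters, then one

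*Protocol article*

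**What the plan says.** Under Methodological considerations and risks, the article gives the length of follow-up a purpose: to "assess long-term outcomes and detect relapse effects, most outcome measures will be collected for a range of 3–12 months post-intervention".

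The Fig. 3 legend sets the layout: "Each sequence comprises a 3- to 12-month baseline control condition, a 3-month intervention transition period, and a 3- to 12-month intervention exposure condition". The Phase 3 study design section describes the post-intervention collection period as "lasting between 3 and 12 months, depending on the cluster", and the Randomisation section says "Each cluster will be randomly allocated to one of four starting dates for implementation". There are four clusters, so each start date has one cluster.

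On analysis, the Phase 3 study design section says "Data gathered during the pre-intervention phase will be directly compared with data collected post-implementation". The statistical methods section for effectiveness and clinical outcomes says "Comparisons within and across clusters will be conducted using the generalised linear mixed model (GLMM) approach", and then "The model will account for the random effect of the cluster and will adjust for relevant confounders, identified in the descriptive analyses, as fixed effects". Table 3 sorts collection into control, implementation and intervention only. The article names no time-since-rollout term and no late-versus-early contrast.

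The one other durability measure is in the implementation fidelity section (H7): continued use of the training programme, and the proportion of nurses who report using the framework at 6 months or later.

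**The concern.** Detecting relapse means comparing the effect late after rollout with the effect soon after it. A single intervention-versus-control contrast averages over exposure time, so it cannot show a decline. The average is also uneven, because follow-up length is fixed by rollout order: every cluster supplies the early months and only the first-starting cluster supplies the last ones.

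Reversion to former practice is an obvious way for a training-based intervention to fail, and the article anticipates it. The dissemination section plans to take results to national agencies to influence practice, policy and education. A reader of the final report could take one pooled benefit, collected over up to 12 months, as evidence that the benefit lasts 12 months.

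**Working it through.** **Inputs.** Four clusters and four start dates (Randomisation). A 3-month transition, with 3–12 months of control and 3–12 months of exposure (Fig. 3 legend). A window from 1 July 2026 to about 31 December 2027 (Trial status), which is 18 months or six quarters. ICC 0.03 (Sample size). A 20% reduction (H1, Table 1) for illustration. Assumed: equal 3-month steps and equal cluster-quarter sizes, with transition quarters left out.

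**Step 1: reproduce the stated range.** Sequence *k* has 3*k* months of control, 3 of transition and 18 − 3*k* − 3 = 15 − 3*k* of exposure. For *k* = 1 to 4 this gives 12, 9, 6 and 3 months, which matches the stated 3–12.

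| Sequence | Q1 | Q2 | Q3 | Q4 | Q5 | Q6 |
|---|---|---|---|---|---|---|
| 1 | C | T | E1 | E2 | E3 | E4 |
| 2 | C | C | T | E1 | E2 | E3 |
| 3 | C | C | C | T | E1 | E2 |
| 4 | C | C | C | C | T | E1 |

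(C control, T transition, E1–E4 exposure months 1–3, 4–6, 7–9, 10–12.)

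Clusters supplying E1, E2, E3 and E4: 4, 3, 2 and 1. E3 and E4 fall only in calendar quarters 5 and 6, where no cluster is in control.

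**Step 2: weights with the terms listed (cluster, no calendar period).** With *c* control and *e* exposed quarters, a cluster's pre/post difference is weighted by *ce*/(*c* + *e*). The (*c*, *e*) pairs are (1,4), (2,3), (3,2) and (4,1), giving 0.8, 1.2, 1.2 and 0.8. These sum to 4, so the shares are 0.2, 0.3, 0.3 and 0.2. Spread over its exposed quarters, each cluster gives 0.05, 0.10, 0.15 and 0.20 per quarter.

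- E1: 0.05 + 0.10 + 0.15 + 0.20 = 0.50
- E2: 0.05 + 0.10 + 0.15 = 0.30
- E3: 0.05 + 0.10 = 0.15
- E4: 0.05

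**Step 3: weights if calendar-period terms are added.** Least squares on the same 20 cells gives these weights on the exposed cells:

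- E1: 1/2 + 1/3 + 1/6 + 1/4 = 1.25
- E2: 1/6 + 0 + 1/12 = 0.25
- E3: −1/6 − 1/12 = −0.25
- E4: −0.25

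A random cluster effect at ICC 0.03 with 1,000–3,000 admissions per cell gives the same weights to within rounding (1.245 to 1.248 on E1, 0.25 on E2, −0.247 to −0.249 on E3 and E4). Across smaller cells (down to 10), cluster autocorrelation of 0.8 or 0.95, monthly periods and a 17-month window, the two late weights stay between −0.12 and −0.25.

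**Step 4: an illustrative relapse.** True reduction 20% in months 1–6 and zero in months 7–12; the average over the four quarters is 10%.

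| Model | Additive scale | Log scale |
|---|---|---|
| No period terms | (0.50 + 0.30) × 20 = 16% | 1 − 0.8^0.8 = 16% |
| Period terms | (1.25 + 0.25) × 20 = 30% | 1 − 0.8^1.5 = 28% |

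A sustained 20% gives 20% in both models.

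**Step 5: can relapse be examined on this layout?** A model with separate E1–E4 effects plus calendar period is estimable. Standard errors relative to the single period-adjusted effect are about 1.14 (months 1–3), 1.47 (4–6), 1.89 (7–9) and 2.4 (10–12). For months 10–12 minus months 1–3 the ratio is 1.6.

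**The case against.** **An analysis plan that is not shown could add exposure-time terms.** The article does not write out the intervention term, so a single effect is read from the pre/post description and the listed terms. This stands as a caution about the model. It does not touch the layout: no analysis plan can change the fact that months 10–12 come from one cluster and that months 7–12 have no concurrent control.

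**The relapse sentence is about data collection, not about the primary estimate.** This is fair in part. Longer collection is necessary for any look at relapse, and Step 5 shows that the data allow one. A reader might infer that the trial cannot examine relapse at all. That goes too far: it can, with low precision.

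**Inflation is not a property of the model as listed.** This stands. A reader might infer that the stated analysis would exaggerate the benefit beyond its peak. The listed terms do not include calendar period, and without it the example gives 16%, below the early 20%. Inflation above the peak arises only if period terms are added.

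**Durability is covered by the H7 sustainability measure.** Only partly. Nurse-reported use is self-report and not a patient outcome, and the last cluster, with 3 months of exposure, cannot supply a 6-month figure within the window.

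**Making the early exposure-time effect the primary result would be costly.** This also stands. The standard error would be about 1.14 times as large for months 1–3 and 1.25 times for the months 1–6 average. If the single period-adjusted effect had 80% power, power would fall to Φ(2.80/1.14 − 1.96) ≈ 69% and Φ(2.80/1.25 − 1.96) ≈ 61%. It would also headline the peak of an effect that may fade. The primary effect should therefore stay.

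**Conclusion.** The point holds as a mismatch between a stated purpose and the analysis and layout described. The terms listed would conceal a relapse: in the example, about 16% reported against a 12-month average of 10%. With the period terms usual in a stepped wedge, the same relapse would be reported as 28–30%, above any effect achieved. That second result is conditional and should not be attributed to the model as written.

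Evidence on patient outcomes beyond 6 months is weak by design, with two clusters for months 7–9, one for months 10–12 and no concurrent control for either.

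The figures assume equal 3-month steps (inferred, because Fig. 3 is not shown), equal cluster-quarter sizes and a linear approximation to the planned models. The Sample size section ends record data on 1 December 2027. That 17-month window gives 11, 8, 5 and 2 months of exposure; the late weights remain negative (−0.25 and −0.19) and months 10–11 still come from one cluster.

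**What to change.** 1. Keep the planned primary effect for H1–H3.
2. Add a pre-specified secondary analysis for H1–H3 with separate effects for months 1–3, 4–6, 7–9 and 10–12 since the end of transition, alongside calendar period. Report the effect by quarter and a late-minus-early contrast, and use both to interpret the primary estimate.
3. Label months 7–9 (two clusters) and 10–12 (one cluster) as descriptive.
4. Reword the sentence under Methodological considerations and risks so that relapse is claimed only for the range that several clusters cover. State that durability of patient outcomes beyond 6 months is weakly supported, and that the H7 measure of use at 6 months or later is self-reported.

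No new data are needed, and recruitment is scheduled to begin only in July 2026. The cost is a little more analysis, late estimates that will be imprecise (the standard error ratios in Step 5), and a narrower durability claim.

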### Trial status

All ethical and governance approvals are in place at participating hospitals. The protocol is Version 5.0 dated 30th April 2025. Recruitment is scheduled to begin on the first of July 2026 and will be completed approximately on 31 st December 2027. The trial is prospectively registered with the Australia New Zealand Clinical Trial Registry ACTRN12625000639426 (registration date: 17/06/2025).

## Conclusion

Nurse-led frameworks improve patient outcomes; however, there is a paucity of standardised evidence-informed nursing frameworks used in the hospital inpatient setting. This contributes to increased preventable adverse events in Australian hospitals, leading to unintentional harm, death and healthcare costs. Based on previous application of HIRAID®, it is anticipated that the HIRAID® in the inpatient setting will provide a nursing framework that will be person-centred, fit-for-purpose and facilitate the assessment of the entire patient. Empowered with this tool, nurses will be able to deliver high-quality care and be better equipped to make sound and evidence-informed decisions.

## Data Availability

Not applicable.

## Abbreviations

AHPEQS: Australian Hospital Patient Experience Question Set
BCW: Behaviour Change Wheel
CNC: Clinical Nurse Consultant
CNE: Clinical Nurse Educator
ED: Emergency department
eMR: Electronic medical record
EN: Enrolled nurse
HACs: Hospital-acquired complications
HIRAID®: History including Infection risk, Red flags, Assessment, Interventions, Diagnostics, communication and reassessment
HREC: Human Research Ethics Committee
ISLHD: Illawarra Shoalhaven Local Health District
NHMRC: National Health and Medical Research Council
NSW: New South Wales
NUM: Nurse Unit Manager
PES-NWI: Practice Environment Scale of the Nursing Work Index
RE-AIM: Reach, Effectiveness, Adoption, Implementation (dose/fidelity) and Maintenance/Sustainability
RN: Registered nurse
RRT: Rapid Response Team
SW-cRCT: Stepped-wedge cluster randomised control trial
TDF: Theoretical Domains Framework
WSLHD: Western Sydney Local Health District
